## Abstract

**Background:**

Denture adhesives, characterized as medical products in 1935 by the American Dental Association, have been considered useful adjuncts for improving denture retention and stability. However, many dentists in Japan are hesitant to acknowledge denture adhesives in daily practice because of the stereotype that dentures should be inherently stable, without the aid of adhesives. The aim of this study is to verify the efficacy of denture adhesives to establish guidelines for Japanese users. The null hypothesis is that the application of denture adhesives, including the cream and powder types, or a control (isotonic sodium chloride solution) would not produce different outcomes nor would they differentially improve the set outcomes between baseline and day 4 post-application.

**Methods:**

This ten-center, randomized controlled trial with parallel groups is ongoing. Three hundred edentulous patients with complete dentures will be allocated to three groups (cream-type adhesive, powder-type adhesive, and control groups). The participants will wear their dentures with the denture adhesive for 4 days, including during eight meals (three breakfasts, two lunches, and three dinners). The baseline measurements and final measurements for the denture adhesives will be performed on the first day and after breakfast on the fourth day. The primary outcome is a general satisfaction rating for the denture. The secondary outcomes are denture satisfaction ratings for various denture functions, occlusal bite force, resistance to dislodgement, masticatory performance, perceived chewing ability, and oral health-related quality of life. Between-subjects comparisons among the three groups and within-subjects comparisons of the pre- and post-intervention measurements will be performed. Furthermore, a multiple regression analysis will be performed. The main analyses will be based on the intention-to-treat principle. A sample size of 100 subjects per group, including an assumed dropout rate of 10 %, will be required to achieve 80 % power with a 5 % alpha level.

**Discussion:**

This randomized clinical trial will provide information about denture adhesives to complete denture wearers, prosthodontic educators, and dentists in Japan. We believe this new evidence on denture adhesive use from Japan will aid dentists in their daily practice even in other countries.

**Trial registration:**

ClinicalTrials.gov NCT01712802. Registered on 17 October 2012.

## Background

The first application of denture adhesive was reported in 1913 [1]. Hence, historically, denture adhesives have already been on the market for over 100 years. Denture adhesives, characterized as medical products in 1935 by the American Dental Association Council on Dental Materials, Instruments, and Equipment, have been considered useful adjuncts for improving denture retention and stability. However, most dentists in Japan do not acknowledge denture adhesives for several reasons. First, they believe that dentures should be stable inherently, without the aid of products such as denture adhesives. Second, famous reports have claimed that denture adhesives ruin dentures, cause shrinkage, and are harmful for denture wearers [2–5], although the quality of these studies is limited (graded as level 4 on the Oxford Levels of Evidence: does not permit clinicians to engage in evidence-based clinical decision-making) [6]. Finally, Japan has no guidelines for using denture adhesives. Consequently, Japanese dentists tend to prohibit denture wearers from using denture adhesives even though these individuals suffer from unstable dentures; moreover, many of these individuals are unable to visit a dental clinic owing to physical disabilities. Furthermore, Japanese researchers are hesitant to conduct clinical trials with denture wearers given the negative attitudes regarding denture adhesives. Thus, patients may use dental adhesives at home without understanding their effects, while dentists will not acknowledge denture adhesives without knowing their effects.

In our aging society, the number of older individuals who are unable to attend dental clinics to receive professional care is increasing. Thus, they cannot receive treatment to adjust their existing dentures or to obtain new dentures with good retention and stability, which is achieved by fitting the denture’s tissue surface to the alveolar mucosa and by sealing the peripheral border [7, 8]. Loose complete dentures can become dislodged when talking or eating, and this may induce anxiety in denture wearers, compelling them to withdraw from social activities, thus decreasing their quality of life [7]. Such patients use denture adhesives even though there are other available treatments, such as existing denture adjustment or new denture fabrication. The continuing marked increase in denture adhesive sales, which reached 12 billion yen in Japan in 2008 [9], suggests that patients use denture adhesives as an acceptable alternative to dentist-applied denture treatments. However, the use of denture adhesive remains controversial in Japan.

We reviewed the literature on denture adhesive use in patients with complete dentures when drafting the trial protocol presented herein. The effectiveness of denture adhesives has been investigated in terms of prosthesis retention, stability, masticatory function, and oral health-related quality of life (OHR-QoL). Several studies demonstrated that the retention and stability improvements were more obvious in old or ill-fitting dentures when compared to new prostheses [10–12]. However, Grasso et al. did not report any differences in adhesive-related retention and stability improvement between well-fitting and ill-fitting maxillary dentures [13]. A study by Figueiral et al., which employed vertical tensile tests and intraoral resistance transducers, showed that denture adhesives did improve maxillary complete denture retention; however, the fit of the prostheses was not reported [14]. Kapur reported that despite showing initial improvements in retention, mandibular denture wearers demonstrated significant loss of retention when asked to chew test foods and drink taste solutions [15]. Regarding bite force, several studies indicated that denture adhesives significantly improve the denture-related bite force [11, 13, 16, 17]. Using a multichannel magnetometer tracking system, Rendell et al. evaluated the effects of denture adhesives on the chewing rates in complete denture patients and found that the mean chewing rates increased immediately after the adhesive was applied and were still increased at 2 and 4 h after application [18]. Kulak et al. examined whether adhesives improve chewing ability, comfort, retention, and patient confidence using subjective measures and found positive correlations concerning the improvements after adhesive use [19]. Nicolas et al. reported that after 3 months of wearing new complete dentures, adhesives improved the subjects’ abilities to manage conventional dentures and enhanced their oral quality of life [20]. Despite the variety of studies on the use of denture adhesives, whether adhesives are beneficial to denture wearers remains controversial.

After reviewing articles selected from the National Library of Medicine’s PubMed database, Cochrane Collaboration Library, ADA Center for Evidence-Based Dentistry website, and EMBASE database, the American College of Prosthodontists published guidelines on denture adhesives [21]. The guidelines stated the following regarding the advantages of denture adhesives: (1) denture adhesives, when properly used, can improve the retention and stability of dentures and help keep food particles from accumulating beneath the dentures, even in well-fitting dentures, and (2) in a quality-of-life study, patient ratings showed that denture adhesives may improve the denture wearer’s perceptions of retention, stability, and quality of life. However, randomized controlled trials (RCTs) for denture adhesives, which can provide evidence in support of the efficacy of denture adhesives and aid in the development of denture adhesive guidelines, are rare, suggesting that even the published guidelines require further development.

While a few clinical trials have been published in Japan, they were not RCTs. Moreover, the results derived from Japanese denture wearers might be different from those mentioned in previous studies performed in other countries since patients’ attitudes toward dental materials reflect food culture and socioeconomic differences among the countries. Therefore, guidelines or official statements concerning the use of denture adhesives in clinical practice in Japan cannot be developed at this time. Performing RCTs and collecting data that can be used to develop clinical practice guidelines to standardize the usage, raise the quality of care, and reduce the risk for older Japanese individuals is essential, since there are many older individuals in Japan who cannot receive denture treatment in a dental clinic owing to their physical conditions, meaning they may turn to dental adhesives instead. Thus, we plan to perform an RCT at the following ten centers: Iwate Medical University, Tohoku University, Tokyo Medical and Dental University, Nihon University School of Dentistry at Matsudo, Tsurumi University, Kanagawa Dental College, Osaka Dental University, Tokushima University, Nagasaki University, and Kagoshima University. This ten-center RCT, which will be performed throughout Japan, has external validity. This trial is referred to as the Denture Adhesive Guideline (DAG) project. The aim of the DAG trial is to verify the efficacy of denture adhesives in order to establish guidelines for using denture adhesives in clinical practice in Japan. The null hypothesis of this study is that the application of two types of denture adhesives (cream and powder) and a control would not produce differences in the set outcomes and would not result in differences in the improvement of the set outcomes between baseline and day 4 following application.

### Inclusion and exclusion criteria

#### Inclusion criteria

To be included in the study, the participant must be completely edentulous, willing to undergo new complete denture treatment, and willing to visit the clinic for denture adjustments as a recall patient. The protocol does not limit the inclusion of participants based on the type of chief complaint, such as pain, looseness, speech, and esthetics, among others.

#### Exclusion criteria

Participants are excluded if they: (1) are ≥90 years of age, (2) have any serious systemic illnesses that may make participating in the study difficult, (3) are unable to understand and respond to the questionnaires used in the study, (4) wear metal-based complete dentures, (5) use denture adhesives regularly, (6) have maxillofacial defects covered by prosthetics, (7) use a tissue conditioner, and/or (8) have severe oral dryness (dryness score ≤20).

### Sample size calculation

A between-group difference of 29 mm on the visual analog scale (VAS) ratings for general satisfaction was considered a meaningful difference. By using variances of 20 mm in the intervention groups and 23 mm in the control group, which were based on previously reported data [22, 23], 100 subjects per group, including an assumed dropout rate of 10 %, will be required to achieve 80 % power with an alpha level of 5 %.

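### The printed inputs (29 mm difference, spreads of 20 and 23 mm, 80% power, 5% alpha) require about 10 evaluable patients per group, so they cannot be reconciled with 100 per group

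*Protocol article*

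**What the plan says.** The section on sample size calculation sets the target: "A between-group difference of 29 mm on the visual analog scale (VAS) ratings for general satisfaction was considered a meaningful difference". It takes "variances of 20 mm in the intervention groups and 23 mm in the control group" from earlier published data. From these it derives "100 subjects per group, including an assumed dropout rate of" 10%, and says that this number "will be required to achieve 80"% "power with an alpha level of 5"%.

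The abstract (Methods) repeats the result without the difference or the spreads: "A sample size of 100 subjects per group, including an assumed dropout rate of" 10%, again for 80% power at 5% alpha. Neither place names the test, the sidedness or a multiplicity adjustment. Neither gives another reason for the number, such as secondary outcomes, subgroups or interim looks.

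The statistical analysis section plans a one-way analysis of variance with Tukey-Kramer comparisons. The alternative is a Kruskal-Wallis test with Bonferroni-adjusted Mann-Whitney tests. Significance is declared at p<0.05.

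**The concern.** All the ingredients of the calculation and its answer are printed, and they disagree by a factor of at least five. A 29 mm difference against a standard deviation of about 21.6 mm is a standardised effect of about 1.35, which a small trial detects. It cannot require 90 evaluable patients per group for 80% power.

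Two things are at stake. The stated power does not belong to the stated difference, so a reader cannot tell what the trial was designed to detect. The meaningful difference is also the natural yardstick for a result intended to support a national guideline. If that figure is in doubt, so is any statement that an effect is or is not large enough to matter.

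The word variances is a second, smaller fault: a variance on this scale would be in mm squared, not mm.

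**Working it through.** **Inputs, all from the sample size section.** Difference 29 mm; spreads 20 mm (each adhesive) and 23 mm (control); power 80%; alpha 5%; dropout 10%; equal groups. Sidedness is not stated, and two-sided is assumed here.

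**The plan's own figure.** 100 per group × 0.9 = 90 evaluable per group.

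**1. Spreads read as standard deviations, adhesive against control.**

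n = (z₀.₉₇₅ + z₀.₈₀)² × (SD₁² + SD₂²) / difference²
= (1.960 + 0.842)² × (20² + 23²) / 29²
= 7.849 × 929 / 841 = 8.67, so 9 evaluable, or 9/0.9 = 10 with dropout.

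With the t distribution (common SD √(929/2) = 21.55 mm), power is 0.764 at n = 9 and 0.812 at n = 10. That is 10 evaluable, or 12 with dropout.

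**2. Adjusted for three pairs.** With alpha 0.05/3, t-test power is 0.796 at n = 13 and 0.833 at n = 14. That is 14 evaluable, or 16 with dropout.

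**3. Other reasonable tests at 80% power.**

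| Variant (two-sided where that applies) | Evaluable per group | With 10% dropout |
|---|---|---|
| Three-group F test, several mean patterns, SD 21.05 to 23 | 9 to 14 | 10 to 16 |
| Mann-Whitney (efficiency 0.864), Bonferroni, SD 21.55 | 17 | 19 |
| Mann-Whitney (efficiency 0.864), Bonferroni, SD 23 | 18 | 20 |

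One-sided variants go as low as 7 with dropout. No variant at 80% power exceeds 20. By the normal formula, even 95% power with Bonferroni and SD 23 gives only 24 with dropout.

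**4. Spreads read literally as variances.** 7.849 × (20 + 23) / 841 = 0.40 per group.

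**5. What would make 90 evaluable correct for 29 mm?** SD = 29 / (2.802 × √(2/90)) = 69 mm. On a 0 to 100 mm scale an SD cannot exceed about 50 mm, so no value of the spread rescues the figure.

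**6. What 90 evaluable per group delivers for 29 mm.** The standard error of an adhesive-control difference is √(929/90) = 3.213 mm. Then 29/3.213 = 9.03 standard errors, and power exceeds 99.9999%.

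**7. Difference detectable with 80% power at 90 per group, before any allowance for interim looks.**

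- Unadjusted, two-sided 5%, adhesive against control: 2.802 × 3.213 = 9.0 mm.
- Tukey-Kramer pools the variance over three groups: (400 + 400 + 529)/3 = 443. The standard error used by the test is √(2 × 443/90) = 3.138 mm, and the critical value is 2.357. The smallest significant difference is 2.357 × 3.138 = 7.4 mm.
- Adhesive against control: 7.39 + 0.842 × √(929/90) = 10.1 mm.
- Cream against powder: 7.39 + 0.842 × √(800/90) = 9.9 mm.

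**8. A difference that does reproduce 100.** For 9 mm: 7.849 × 929 / 81 = 90.02, and 90.02/0.9 = 100.02 per group.

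**The case against.** The strongest reply is that no harm is done. Against 29 mm the trial is over-powered, no patient enters an inadequate study, and allocation and analysis stay as they are. That stands as far as it goes. A reader who sees a false power statement might infer that the trial is too small, and the arithmetic shows the opposite. It does not make the derivation right: the text says that 100 per group are required for 80% power, and they are not.

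A second reply is that the extra patients serve subgroups, secondary outcomes or the two interim looks, or that a fuller document explains the number. Neither the sample size section nor the abstract gives such a reason. The inflation for two looks was not computed, but it would have to be at least fivefold, which is not plausible. Nor is this a gap left by condensation, because the inputs and the answer are both printed and conflict.

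Three stronger readings are tempting and go beyond the document:

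- **That 29 is a misprint for 9.** The match at 9 mm is close and a one-digit slip is plausible, but nothing in the text says so.
- **That the sponsor sized the trial for a quarter or a third of its own meaningful difference.** This takes 29 mm as certainly intended. If 9 mm was meant, the design is coherent and one number is misprinted.
- **That the calculation ignored the Tukey-Kramer adjustment.** The sample size section names no test. A calculation that cannot be reproduced cannot be shown to have left something out.

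**Conclusion.** The point holds as an irreconcilable set of figures. The printed inputs require about 10 evaluable patients per group (14 with Bonferroni for three pairs), and about 10 to 20 including dropout across reasonable tests, against the stated 100. With 90 evaluable, power for 29 mm is essentially 100%, not 80%. The difference that the trial was sized for cannot be recovered from the document.

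This rests on reading 20 and 23 mm as standard deviations, which the unit forces, and on a two-sided test, which is assumed. A one-sided test widens the gap. The detectable differences of 9.0, 10.1 and 9.9 mm assume those standard deviations and make no allowance for the looks after 100 and 200 completers. They should therefore not be presented as holding at an overall 5% level.

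Whether 7 to 10 mm matters to patients cannot be judged from the document. The finding is not that the trial is underpowered or should be made smaller.

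**What to change.** Keep 300 patients. In the sample size section:

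1. State the difference actually used in the calculation, and confirm separately which difference is regarded as meaningful.
2. Replace variances with standard deviations.
3. Name the test, its sidedness and any adjustment for the three pairwise comparisons.
4. Restate the power so that it follows from these inputs, and make the abstract agree.

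If the number was fixed at 100 and the power is to be described from it, the following wording would be accurate: With 90 evaluable patients per group and standard deviations of 20 mm (adhesives) and 23 mm (control), and before any adjustment for the interim analyses, the trial has 80% power to detect about 10.1 mm between an adhesive and control and about 9.9 mm between cream and powder (Tukey-Kramer). For an unadjusted two-sided 5% comparison of an adhesive with control, the figure is about 9.0 mm.

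If 29 mm is confirmed as meaningful, add that estimates and confidence intervals will be read against it. An observed difference of about 7.4 mm, 7.4/29 = 26% of that value, would already reach Tukey significance.

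The cost is rewording one paragraph and one sentence of the abstract, after the sponsor checks its original calculation. Recruitment, allocation and analysis are unchanged.

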### Interim analyses and early stopping of the clinical trial

The data and safety of the clinical trial will be monitored. Interim analyses of the trial will be performed when 100 and 200 participants have completed the trial. The trial will be stopped under the following conditions: (1) excess harm is observed, (2) statistically significant benefits are observed, (3) little additional useful information or negligible chance of demonstrating efficacy will be yielded if fully completed. These early stopping rules will help minimize harm and maximize the benefits for the patients enrolled in the RCT.

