### Statistical analysis

First, analyses of normality using the Kolmogorov–Smirnov test will be performed for all variables. When normality can be verified, parametric tests will be performed. However, if normality cannot be verified, then two types of analyses will be performed, as follows: (1) the distributions of the dependent variables will be normalized by the appropriate transformations for parametric tests, or (2) nonparametric tests will be performed.

The between-subjects comparisons among the three groups will be performed using one-way analyses of variance with Tukey-Kramer post hoc tests or Kruskal-Wallis tests with Mann-Whitney *U* tests adjusted with the Bonferroni correction. The within-subjects comparisons of the pre- and post-intervention measurements will be performed by either paired *t* tests or Wilcoxon signed-rank tests. Furthermore, the multiple regression analysis will be performed using the abovementioned covariates as predictors.

Subgroup analyses will also be undertaken among the different subpopulations defined by each of the multiple baseline characteristics of the participants in order to study whether the effects of the intervention vary across these patient characteristics.

All of the analyses will be performed in accordance with the intention-to-treat principle, and various strategies to account for any post-randomization missing data will be contemplated. However, in the sensitivity analyses, we will also perform per protocol analyses to assess the robustness of our findings with regard to potential incomplete adherence; in particular, patients with major protocol violations or poor adherence will be excluded.

All statistical analyses will be performed using the IBM SPSS Statistics Package v21 (IBM, Armonk, NY, USA). A *p* value of <0.05 will be considered statistically significant.

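### Interim efficacy stopping at 100 and 200 participants has no significance level other than p<0.05, so the stated 5% alpha does not hold (about 7 to 11% as written)

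*Protocol article*

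**What the plan says.** The section on interim analyses and early stopping fixes the schedule: "Interim analyses of the trial will be performed when 100 and 200 participants have completed the trial". It lists three grounds for stopping: harm, futility, and that "statistically significant benefits are observed". It gives no numerical threshold for any of them, and names neither the outcome nor the group comparison that the efficacy ground refers to.

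The Statistical analysis section closes with a general rule that a p "value of <0.05 will be considered statistically significant". No other level appears in the article. The same section plans one-way ANOVA with Tukey-Kramer, or Kruskal-Wallis with Bonferroni-corrected Mann-Whitney tests, to compare the three groups.

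The Sample size calculation section says that 100 per group "will be required to achieve 80 % power with an alpha level of 5" per cent. The abstract repeats that alpha.

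**The concern.** The article fixes how many looks there are, when they occur, that statistical significance triggers a stop, and what statistical significance means. Put together, these give three chances to declare benefit at the same unadjusted level. Each extra look adds false-positive probability, so the 5% used to size the trial is no longer the error rate of the procedure described.

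The Tukey-Kramer and Bonferroni steps do not help. They protect the three pairwise comparisons within one analysis and do nothing across analyses.

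The stake is the credibility of a positive result. The trial is meant to support national guidance on denture adhesives. A benefit declared at an interim look under this rule would carry a higher false-positive risk than the report would state.

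**Working it through.** **Inputs.** Looks at 100, 200 and 300 participants, so information fractions of about 1/3, 2/3 and 1 (interim analyses section). Equal allocation, so about 33, 67 and 100 per arm (randomization section). Threshold p<0.05 (Statistical analysis section). Two-sided testing is my assumption, because the article does not state sidedness.

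**The plan's own figure.** With a single analysis at 100 per arm, simulation (200,000 replicates) gives 5.05% for the ANOVA F test and 5.05% for Tukey-Kramer. The stated 5% is therefore right for one look.

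**Three looks, one comparison.** The cumulative statistics Z1, Z2, Z3 are jointly normal with correlation √(t_i/t_j), where t = 1/3, 2/3, 1.
- Two-sided stopping: P(any |Z| > 1.96) = 0.107. The two interims alone give 0.083. If 10% drop out and the final analysis has 270 evaluable, the total is 0.104.
- Benefit direction only: P(any Z > 1.96) = 0.0536, against 0.025 for one look.
- Benefit-only interims and a two-sided final test: 0.0536 + 0.025 = 0.0786, about 7.9%.

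**Three looks, three arms, Tukey-Kramer at each look (simulation).**
- Two-sided at every look: 10.7 to 11.0%. The ANOVA F test gives 10.6 to 11.0%.
- Stop at an interim only if an adhesive beats control, with any pairwise difference counting at the end: about 7.1%.

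| Reading of the rule | Overall type I error |
|---|---|
| One look | 5% |
| Benefit-only interims, two-sided final | 7.1% (Tukey) to 7.9% (single comparison) |
| Two-sided at all looks | 10.7% (single comparison) to 11.0% (Tukey) |

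**Do standard boundaries repair it?** The O'Brien-Fleming constant for three equal looks is 2.004. The critical values are 2.004·√(3/k) = 3.47, 2.45 and 2.00 for k = 1, 2, 3, which correspond to nominal two-sided p of 0.0005, 0.0141 and 0.0451. Applied to Tukey-adjusted p values, the rounded levels give about 5.0% family-wise. Haybittle-Peto (0.001, 0.001, 0.05) also gives about 5.0%.

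**Illustration under an assumed effect.** The article reports "variances of 20 mm in the intervention groups and 23 mm in the control group". As these are in mm, I read them as standard deviations: root mean square √((20² + 23²)/2) = 21.55 mm. At 33 per arm the standard error of a difference is 21.55·√(2/33) = 5.31 mm. Significance then needs an observed difference of about 10.6 mm, or 12.6 mm with Tukey. Suppose the true difference were 9 mm. This is my assumption and is not in the article; it is roughly what 90 per group detects with 80% power. The chance of crossing p<0.05 at the first look would be about 25% with Tukey, since Φ((9 − 12.6)/5.31) = Φ(−0.68) = 0.25, and about 39% unadjusted. With the O'Brien-Fleming level it falls to about 1% with Tukey, or 4% for a single comparison.

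**The case against.** The strongest reply is that the link to p<0.05 is inferred. The interim section gives no number, the p<0.05 sentence is general and does not mention interim looks, and an analysis plan or monitoring charter that is not shown may hold a boundary. Part of this stands: one cannot assert that the trial has no boundary. But the article does more than stay silent. It makes statistical significance the trigger and gives that term a single definition. If a boundary exists elsewhere, the article misdescribes the rule and still needs correcting.

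A second reply is that stopping is for benefit, so counting interim stops in both directions overstates the error. This also stands, and is why the range starts at about 7%. It does not remove the problem, since the benefit-direction error still roughly doubles. Binding futility or harm rules would lower the error somewhat, but no thresholds are given for them.

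Three stronger readings are tempting and are not supported:
- *The error rate simply doubles.* That holds for two-sided stopping, or for the benefit direction alone in a single comparison, but not for every reading of the rule.
- *The error could reach 18 to 19%.* That is the result if either adhesive were tested against control with no adjustment at each look. The article plans adjusted comparisons.
- *The missing boundary would end the trial at 100 participants under the 29 mm difference.* A true 29 mm would indeed cross p<0.05 at the first look almost surely, but it would also cross the O'Brien-Fleming level there about 94 to 98% of the time. The cause is a separate inconsistency in the sample size: 2·21.55²·(1.96 + 0.84)²/29² gives 9 per group, not 100. The article also presents 29 mm as a meaningful difference, not as the expected effect.

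**Conclusion.** The point holds. The interim rule, the single significance level and the 5% alpha cannot all stand as written. Overall type I error is about 7 to 8% if the interims stop only for benefit and the final test is two-sided, and about 11% if stopping is two-sided. For a single comparison the error in favour of benefit goes from 2.5% to about 5.4%.

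This rests on three assumptions: p<0.05 applies at each look because it is the only level given; the looks fall at about one third, two thirds and all of the information; and testing is two-sided at 5%. It does not depend on the 29 mm difference or on the standard deviations.

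**What to change.** Add one paragraph to the interim analyses section and a cross-reference in the Statistical analysis section. It should state that:
- efficacy stopping is judged only on general satisfaction, the primary outcome, using Tukey-Kramer adjusted p values;
- the nominal levels are O'Brien-Fleming (p<0.0005 at 100, p<0.014 at 200, p<0.045 at 300) or Haybittle-Peto (p<0.001 at both interims, 0.05 at the end);
- the general p<0.05 rule does not apply to the interim analyses and, under O'Brien-Fleming, the final primary test uses 0.045;
- any look already taken is reported with its date and result, and the boundary governs the remaining looks.

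If an unseen plan already holds a boundary, cite it and quote its levels instead.

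The cost is a lower chance of stopping early and, with O'Brien-Fleming, a final level of 0.045 rather than 0.05. A boundary controls the error rate. It does not remove the tendency of a trial stopped early to overestimate its effect.
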